## Abstract

**Introduction:**

Sepsis is characterised by a dysregulated immune response to infection, with exaggerated pro-inflammatory and anti-inflammatory responses. A predominant immunosuppressive profile affecting both innate and adaptive immune responses is associated with increased hospital-acquired infection and reduced infection-free survival. While hospital-acquired infection leads to additional antibiotic use, the role of the immunosuppressive phenotype in guiding complex decisions, such as those affecting antibiotic stewardship, is uncertain. This study is a mechanistic substudy embedded within a multicentre clinical and cost-effectiveness trial of biomarker-guided antibiotic stewardship. This mechanistic study aims to determine the effect of sepsis-associated immunosuppression on the trial outcome measures.

**Methods and analysis:**

RISC-sepsis is a prospective, multicentre, exploratory, observational study embedded within the ADAPT-sepsis trial. A subgroup of 180 participants with antibiotics commenced for suspected sepsis, enrolled in the ADAPT-sepsis trial, will be recruited. Blood samples will be collected on alternate days until day 7. At each time point, blood will be collected for flow cytometric analysis into cell preservation tubes. Immunophenotyping will be performed at a central testing hub by flow cytometry. The primary outcome measures are monocyte human leucocyte antigen-DR; neutrophil CD88; programmed cell death-1 on monocytes, neutrophils and T lymphocytes and the percentage of regulatory T cells. Secondary outcome measures will link to trial outcomes from the ADAPT-sepsis trial including antibiotic days; occurrence of hospital-acquired infection and length of ICU-stay and hospital-stay.

**Ethics and dissemination:**

Ethical approval has been granted (IRAS 209815) and RISC-sepsis is registered with the ISRCTN (86837685). Study results will be disseminated by peer-reviewed publications, presentations at scientific meetings and via patient and public participation groups and social media.

Strengths and limitations of this studyMulticentre study recruiting a broad cohort of patients, representative of critically ill patients with sepsis in the UK.Centralised flow cytometry immunophenotyping using preservation methods allowing standardisation in the context of multicentre recruitment.Embedded within a clinical trial, immunophenotypes will be linked to robust clinical outcomes.As an observational study, RISC-sepsis will provide insights into the impact of sepsis-associated immunosuppression on a biomarker-guided antibiotic duration intervention but since it is not interventional, it will not offer a robust precision-medicine approach to antibiotic stewardship.

## Introduction

Sepsis is a syndrome of life-threatening organ dysfunction secondary to a dysregulated immune response to an infection.^1^ Mortality from sepsis is high, with 31% of patients dying in hospital and a further 15% of survivors dying in the subsequent year.^2 3^ As a leading cause of death, there are an estimated 31.5 million cases of sepsis worldwide each year.^4^ Organ support in a critical care setting is often required and patients with sepsis account for a third of general adult critical care admissions in the UK.^2^

The dysregulated immune response that characterises sepsis is a paradigm of both a pro-inflammatory and an anti-inflammatory response.^5 6^ While these immune states can occur simultaneously, a predominant immunosuppressive profile has been associated with hospital-acquired infections and mortality.^7 8^ While there is no single test for sepsis-associated immunosuppression, well-established leucocyte cell surface markers identify cellular dysfunction and are associated with adverse clinical outcomes. These dysfunctions are demonstrated across both the innate and adaptive immune responses with the most well-established markers being monocyte human leucocyte antigen-DR (mHLA-DR), neutrophil C5a receptor (CD88), percentage of regulator T cells and programmed cell death-1 (PD-1).^9–12^ The persistence of these cellular abnormalities and the accumulation of dysfunctions increase the risk of adverse clinical outcomes.^10 13–15^

While an immunosuppressive profile has been linked to poor clinical outcomes, the influence that it has in guiding complex clinical decision-making processes, such as those involved in antibiotic stewardship remain uncertain. Antibiotic treatment in sepsis may be life-saving, but the overuse of antibiotics leads to the emergence of antimicrobial resistance (AMR) and adverse clinical outcomes.^16–19^ The optimal duration of antibiotic treatment in sepsis is unknown.^20^ Biomarker-guided antibiotic durations are not recommended for routine use in the UK^21^ and the current evidence for effectiveness is regarded as low quality internationally.^22^ The ADAPT-Sepsis trial (ISRCTN47473244) is a UK National Institute for Health and Care Research (NIHR) Health Technology Assessment-commissioned clinical trial that will evaluate the clinical and cost-effectiveness of procalcitonin (PCT) and C reactive protein (CRP) protocols for biomarker-guided antibiotic duration decisions in a National Health Service setting. This three-arm trial of daily PCT monitoring, daily CRP monitoring or standard of care aims to determine whether the use of these biomarkers reduces total antibiotic use at 28 days (primary superiority outcome), while maintaining treatment safety of 28-day mortality (primary non-inferiority outcome). Investigations into the dynamics of CRP and PCT with mHLA-DR have shown that high levels of CRP or PCT are associated with low expression of mHLA-DR,^23–25^ suggesting CRP and PCT offer a window into the more complex dysregulation of the immune response.

This protocol outlines a mechanistic study embedded within the ADAPT-Sepsis trial. RISC-sepsis will immune phenotype patients using leucocyte surface biomarkers and dichotomise patients into two groups, ‘sepsis-associated immunosuppression’ and ‘non-immunosuppressed’ (definition below). We will then explore the effectiveness of the biomarker-guided antibiotic duration intervention and the impact on trial outcomes for patients with sepsis-associated immunosuppression.

### Rationale

The ADAPT-Sepsis trial will include a heterogeneous population of adult patients with sepsis, including those with sepsis-induced immunosuppression. As a phenotype associated with hospital-acquired infections and reduced infection-free survival, there may be heterogeneity in the effect of the biomarker-guided antibiotic duration intervention for patients with this phenotype. If biomarker-guided antibiotics are ineffective in patients with sepsis-associated immunosuppressed, then a greater degree of patient stratification may be required to ensure optimal antibiotic duration. Furthermore, if CRP and PCT levels fall over the same period that cellular defects resolve, this may give clinicians greater confidence in following biomarker-guided antibiotic durations.

### Research question

Does sepsis-associated immunosuppression render a PCT/CRP biomarker-guided antibiotic duration intervention ineffective?

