### Hypothesis

Sepsis-associated immunosuppression will be associated with longer duration of antibiotics, due to persistently raised PCT and CRP; more hospital-acquired infection and more antibiotic treatment days.

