### Primary objective

To determine differences in ADAPT-sepsis trial outcomes between patients defined as ‘sepsis-associated immunosuppressed’ versus ‘non-immunosuppressed’.

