### Data analysis plan

A formal analysis plan will be finalised and deposited on an open access platform before the database is locked.

For the primary objective, the time it takes for antibiotics to be stopped in patients during the ADAPT-sepsis biomarker-guided antibiotic phase will be summarised and the distribution of the outcome described for the ‘sepsis-associated immunosuppression’ and the ‘non-immunosuppressed’ groups. The mean number of antibiotic days will be compared between groups obtained from linear regression models and adjusted for confounding variables. In addition, each of the cellular markers will be assessed as a continuous outcome. The change in cellular markers between each time point will be correlated with the number of days on antibiotics using Spearman’s correlation coefficient. One sample t tests will be used to assess the changes between time points.

The trial outcomes of 28-day antibiotics, hospital-acquired infections and length of ICU-stay and hospital-stay will be summarised for the ‘sepsis-associated immunosuppressed’ and ‘non-immunosuppressed’ groups. Differences between groups will be assessed using linear regression for continuous variables and logistic regression for categorical variables. We will describe the difference between the groups using p values, point estimates and 95% CIs.

For the secondary objective, we will assess the difference in the PCT/CRP levels and cellular markers for patients who met the criteria for ‘sepsis-associated immunosuppressed’ and when immune profile recovered (ie, became ‘non-immunosuppressed’). Assessments will be captured over time, and we will compute a longitudinal analysis (taking time as a random effect) to assess the difference in the two groups.

Subgroup analyses:

Exploratory analysis will be carried out for the following subgroups:

Patients receiving critical care for a medical versus a surgical cause of sepsis;Patients receiving critical care because of trauma versus non-trauma;Patients receiving critical care because of a community-acquired infection versus a hospital-acquired infection;Infection site: community-acquired pneumonia; hospital-acquired pneumonia; urinary tract infection; intra-abdominal infection or positive blood culture;Patients with septic shock, as defined by persistent hypotension requiring vasopressors to maintain an mean arterial pressure (MAP) ≥65 mm Hg and a serum lactate of >2 mmol/L.^1^

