Regression models will be used with ‘sepsis-associated immunosuppressed’ as an interaction term by subgroup for number of days on antibiotics.

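### The research question asks whether immunosuppression changes the effect of biomarker guidance, but no analysis named in the article compares trial arms within phenotype

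*Protocol article*

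**What the plan says.** The Research question section of the protocol article asks "Does sepsis-associated immunosuppression render a PCT/CRP biomarker-guided antibiotic duration intervention ineffective". The Rationale gives the reason: "there may be heterogeneity in the effect of the biomarker-guided antibiotic duration intervention for patients with this phenotype". The Introduction describes the parent trial as "This three-arm trial of daily PCT monitoring, daily CRP monitoring or standard of care" and says of the substudy: "We will then explore the effectiveness of the biomarker-guided antibiotic duration intervention and the impact on trial outcomes for patients with sepsis-associated immunosuppression".

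The rest of the article sets up a different comparison. The Hypothesis is one of association: "Sepsis-associated immunosuppression will be associated with longer duration of antibiotics, due to persistently raised PCT and CRP", with more hospital-acquired infection and more treatment days. The Primary objective contrasts trial outcomes between the two phenotype groups. The Sample size section powers a 3-day difference between those groups. In the Data analysis plan, "The mean number of antibiotic days will be compared between groups obtained from linear regression models and adjusted for confounding variables", where the groups are the phenotypes, and the other trial outcomes are compared in the same way. The only interaction enters the phenotype "as an interaction term by subgroup for number of days on antibiotics". The subgroups listed are medical or surgical cause, trauma, community- or hospital-acquired infection, infection site and septic shock.

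**The concern.** An intervention is effective or ineffective relative to a comparator. To say that biomarker guidance fails in immunosuppressed patients, one must compare the biomarker arms with standard care inside that phenotype, and compare the result with the same contrast in the other phenotype. A difference in antibiotic days between phenotypes does neither. Sicker or more immunosuppressed patients may have longer courses under any policy, standard care included.

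What is at stake is the conclusion. The Rationale says, conditionally, that further patient stratification may be needed if guidance proves ineffective in this phenotype. If the plan is followed as written, a prognostic difference could be reported as evidence on that point.

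**Working it through.** **1. The plan's own figure.** Inputs from the Sample size section: difference 3 days, SD 6, alpha 5% (sidedness not stated; two-sided fits), power 90%, withdrawal 5%.

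n per group = 2 × (1.96 + 1.28)² × 6² / 3², about 84 to 85, taken as 85. Then 85 / 0.95 = 89.5, rounded up to 90 per group, or 180 in total. The stated 180 reproduces. It powers the phenotype main effect only.

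**2. Does the phenotype contrast identify the answer?** Assume 1:1:1 allocation (the ratio is not given), so two-thirds of each phenotype receive biomarker guidance. Fix the phenotype means at 10 and 7 days, a 3-day difference. Entries are mean days in the biomarker arms / standard care.

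| Scenario | Immunosuppressed | Non-immunosuppressed | Phenotype difference | Interaction |
|---|---|---|---|---|
| Guidance saves 2 days in both | 9.33 / 11.33 | 6.33 / 8.33 | 3.0 | 0 |
| Saves nothing in immunosuppressed, 2 days in the others | 10 / 10 | 6.33 / 8.33 | 3.0 | +2 |
| Saves 2 days only in immunosuppressed | 9.33 / 11.33 | 7 / 7 | 3.0 | −2 |

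The interaction is (biomarker − standard care) in immunosuppressed patients minus the same in the others. All three rows give the planned analysis the same result, though they mean no modification, the feared failure, and the reverse.

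Adding arm as a covariate without an interaction does not separate them. In the second row the within-arm phenotype differences are 10 − 6.33 = 3.67 and 10 − 8.33 = 1.67, and their weighted mean is 2/3 × 3.67 + 1/3 × 1.67 = 3.0.

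**3. What could the interaction show at this sample size?** Evaluable patients: 180 × 0.95 = 171. The immunosuppressed share is not given, so 30% and 50% are shown as assumptions.

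SE = 6 × √(sum of 1/n over the four arm-by-phenotype cells); power = Φ(3/SE − 1.96) for a 3-day interaction.

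- Both biomarker arms vs standard care, 50% share: cells 57, 57, 28.5, 28.5; SE 1.95; power 34%.
- The same, 30% share: cells 34.2, 79.8, 17.1, 39.9; SE 2.12; power 29%.
- One biomarker arm vs standard care, 50% share: four cells of 28.5; SE 2.25; power 27%.
- The same, 30% share: cells 17.1, 39.9, 17.1, 39.9; SE 2.45; power 23%.

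The 95% CI half-width runs from 1.96 × 1.95 = 3.8 days to 1.96 × 2.45 = 4.8 days. For 90% power with the biomarker arms pooled, about 757 (50% share) to 901 (30% share) evaluable patients would be needed.

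**The case against.** The strongest defence is that most of the article is coherent. The abstract's aim, the hypothesis, the primary objective, the sample size and the models all concern association between phenotype and outcomes, and the planned comparison addresses that. The study is labelled exploratory and observational, and its limitations statement concedes that it will not deliver a robust precision-medicine approach. A formal analysis plan is promised before database lock, and the confounders are not named. This stands as a limit on scope: the mismatch lies in the research question, the rationale and the stated intention to explore effectiveness. It does not remove the mismatch. The article itself fixes the objective, the powered contrast and the subgroup list without arm, and arm as one more confounder would not estimate effect modification. The limitations statement does not say that the question goes unanswered.

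Four stronger readings are tempting but unsupported.

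- A reader might infer that arm is used nowhere. The article shows only that it is not named. Arm could be among the unnamed covariates.
- A reader might infer that the powered comparison is itself diluted: if the 3 days arise only in the biomarker arms, the overall difference is 3 × 2/3 = 2 days and power falls from 90% to 58%. That assumes no phenotype difference under standard care. The Sample size section does not tie the 3 days to the biomarker arms, and a difference under standard care is exactly what makes the contrast prognostic.
- A reader might infer that the phenotype should be redefined on the day 1 sample. The article's definition requires abnormalities to persist for 3 or more days, which one sample cannot show.
- A reader might infer that arm does alter the phenotype, because sampling runs to day 7 during the intervention. This is possible, but nothing in the document shows or quantifies it.

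**Conclusion.** The point holds for the research question and the effectiveness claims in the Rationale and Introduction. It does not hold for the hypothesis or the primary objective. No analysis named in the article can tell whether biomarker guidance works less well in immunosuppressed patients, and that does not depend on any assumed figure.

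The power figures do rest on assumptions: 171 evaluable patients and SD 6 follow the article, while 1:1:1 allocation and a 30% to 50% immunosuppressed share are assumed. On that basis the interaction that would answer the question can be estimated, but with only about 23% to 34% power for a 3-day effect.

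**What to change.** Add an exploratory model for antibiotic days with arm, phenotype, arm × phenotype and the planned covariates. Report the biomarker arms versus standard care within each phenotype, and the interaction, all with 95% CIs. State that this analysis is not powered, and give the range above with its assumptions. Describe the phenotype comparison as prognostic only. If the interaction is not wanted, reword the research question as one of association between phenotype and trial outcomes, and bring the related sentences in the Rationale and Introduction into line.

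Keep the article's phenotype definition. Note as a limitation that it uses post-randomisation samples up to day 7 and so could be affected by arm. A sensitivity analysis with the phenotype taken from the day 1 and day 3 samples is optional.

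The cost is wording and one added model before database lock, with no new data. The downside is an imprecise interaction estimate: a wide interval that includes zero must not be read as evidence that guidance works equally well in both phenotypes.

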### Hypothesis

Sepsis-associated immunosuppression will be associated with longer duration of antibiotics, due to persistently raised PCT and CRP; more hospital-acquired infection and more antibiotic treatment days.

### Primary objective

To determine differences in ADAPT-sepsis trial outcomes between patients defined as ‘sepsis-associated immunosuppressed’ versus ‘non-immunosuppressed’.

### Secondary objective

To monitor changes in expression of leucocyte surface markers (primary outcome measures) over the time course of the ADAPT-Sepsis biomarker-guided antibiotic duration intervention period.

## Methods and analysis

RISC-sepsis is a prospective, multicentre, exploratory, observational study embedded within the ADAPT-Sepsis trial.

### Population

We will include sequential patients who are enrolled into the ADAPT-sepsis trial within sites in the RISC-sepsis substudy. Patients are included in the ADAPT-sepsis trial based on the following inclusion criteria:

Hospitalised adult patients at least 18 years of age;Up to 24 hours since initiation of antibiotics for suspected sepsis;Likely to remain hospitalised and requiring intravenous antibiotics for the next 72 hours;Requirement for critical care.

Patients are excluded based on the following criteria:

More than 24 hours since receiving first empiric intravenous antibiotic treatments for suspicion of sepsis;Prolonged (greater than 21 days) antimicrobial therapy mandated (eg, for endocarditis, cerebral/hepatic abscess, tuberculosis, osteomyelitis);Severely immunocompromised (eg, blood neutrophil count less than 0.5×10^9^/L) not caused by sepsis;Any patient given, or anticipated to receive an IL-6 receptor inhibitor drug (eg, tocilizumab or sarilumab) during their acute hospital admission;All treatment for suspected sepsis likely to be stopped within 24 hours of its initiation because of futility;Patient participation declined;Previously enrolled in ADAPT-Sepsis.

### Outcomes

The primary outcomes are markers of blood leucocyte function measured by flow cytometry. These primary markers are:

Monocyte HLA-DRNeutrophil CD88PD-1 on T lymphocytes (CD4-positive and CD8-positive), monocytes and neutrophilsPercentage of regulatory T cells

Secondary outcome measures include outcome measures derived from the ADAPT-Sepsis trial including duration of antibiotics during the ADAPT-Sepsis intervention phase; total antibiotic days measured at 28 days; occurrence of hospital-acquired infection and length of ICU-stay and hospital-stay. Secondary measures will also include PCT and CRP concentrations in serum.

### Sampling and data collection

As a substudy within the ADAPT-Sepsis trial, all RISC-sepsis procedures and sampling will occur within the trial. Sampling will occur during the ADAPT-Sepsis intervention period when blood is sampled daily. While additional blood samples are taken from patients for RISC-sepsis, there is no increase in number of sampling episodes. Patients will have blood sampled on alternate days up to four sampling points (days 1, 3, 5 and 7). Blood for flow cytometric analysis will be collected in Cyto-Chex (Streck, La Vista, USA) blood preservation tubes before shipping to a central testing hub (Newcastle University). Serum will be collected, frozen and stored at site until the end of the recruitment period.

Baseline clinical data and outcome data will be obtained from the ADAPT-sepsis data collection. Baseline data will include admission diagnosis, site of infection, acute physiology and chronic health evaluation (APACHE) II and sequential organ failure assessment scores and sepsis bundle care elements in the first 24 hours. In addition, at each RISC-sepsis sampling point, the circulating white cell count and differential count will be recorded.

### Blood sample analysis

Flow cytometric analysis will be performed on a single centralised (Newcastle University) BD FACSymphony A5 flow cytometer (Becton Dickinson Biosciences, San Jose, California, USA, from here BDB). Daily internal quality control will be performed using Cytometry Setup and Tracking beads (BDB).

Leucocyte staining will be performed using antibody:fluorophore conjugates supplied by BDB. Samples will be processed according to a standard operating procedure.

At each time point, serum will be collected for measurement of PCT and CRP. These will be batched and processed by ELISA at the end of the recruitment period.

### Immune phenotyping

Cells will be identified based on light scatter properties and cellular markers: CD15++neutrophils; CD14+monocytes; CD3+CD4+ T cells; CD3+CD8+ T cells; and CD3+CD4+ CD25+ CD127 lo regulatory T cells. Expression of monocyte HLA-DR, neutrophil CD88 and PD-1 (CD279) on monocytes, neutrophils and T lymphocytes will be measured.

In addition, exploratory analyses will include: CD14+CD16- classical monocytes; CD14+CD16+ intermediate monocytes; CD14− CD16+non-classical monocytes; CD3− CD19+B cells; CD3− CD56+NK cells; CD3− CD19− CD14− CD16− CD56− HLA−DR+dendritic cells. In addition to expression of HLA-DR and CD279 in cell populations, CD274 (PD-L1) will also be measured.

Data will be assessed for evidence of batch effects and normalisation approaches will be used. Expert manual gating will be performed using a predefined gating standard operating procedure. We will report number and percentage of cell populations in blood and median fluorescent intensity of key markers.

